## Abstract

**Purpose:**

The postnatal period is a vulnerable time for parents and children but epidemiological and health care utilisation data for Germany on parental mental health during early childhood is scarce. This protocol describes the rationale, aim and study design of a population-based cohort study to assess the occurrence and determinants of psychosocial stress and mental health disorders, as well as the use and cost of health care and social services in early childhood.

**Methods:**

As part of the collaborative SKKIPPI project, we will contact a random sample of 30,000 infants listed in the residents’ registration offices of three German towns and we expect to include 6,000 mother–child pairs. Both parents are invited to fill out an online screening questionnaire. Mothers with indications of psychosocial stress will be interviewed to assess mental health disorders, regulatory problems of their children, as well as health care and social services utilisation, with a follow-up assessment after 6 months.

**Results:**

After description of sociodemographic and health data, we will analyse occurrences, patterns, and potential determinants (maternal age, social status, household factors, migration status etc.) of psychosocial stress and mental health disorders in the mothers and their children in early childhood.

**Conclusions:**

Our study will identify potential risk and protective factors for postnatal mental health and health care utilization of psychosocially burdened families. This will help to improve prevention and treatment strategies to strengthen the parent–child relationship, to reduce persisting vulnerability of children, and to improve health care and social services.

**Trial registration:**

The study has been registered in the German Clinical Trial Registry on February 8th 2019 (DRKS-ID: DRKS00016653).

## Rationale

Psychosocial stress in parents with young children is not only a burden for their own mental health but may also negatively affect the children’s short and long-term mental well-being [1]. Epidemiological studies on maternal mental health disorders in the postnatal period have been almost exclusively focused on postnatal depression and anxiety disorders [2–4]. For postnatal depression, prevalence estimates revealed large variations worldwide [3, 4]. A meta-analysis based only on studies using the Edinburgh Postnatal Depression Scale (EPDS)—a self-report screening instrument for postnatal depression [5]—assessed a global prevalence of almost 18% [4]. An international review including also studies using psychiatric interviews revealed prevalences ranging from 4 to 64% [3]. According to another systematic review, the prevalence of self-reported postnatal anxiety symptoms was 15% and of clinically diagnosed anxiety disorders around 10% [2]. The few German studies assessing prevalence data on postnatal maternal mental health disorders revealed estimates between 3 and 6% for postnatal depression and around 11% for postnatal anxiety [6–8]. Ongoing research is focusing especially on postnatal depression or anxiety disorders, but there are less studies assessing prevalence data of other postnatal mental health problems like obsessive–compulsive disorders [9, 10] or parental burnout, a concept that has only recently been suggested and investigated [11, 12]. One of the few studies in this field reported that 10.4% of the parents with at least one child at home belonged to an average parental burnout category and 2.1% of the parents to a high parental burnout category, but the sample included parents with children of all ages [13].

Various stressors for an elevated risk of postnatal depression and anxiety disorders have been identified. These include a history of previous depression, single marital status, lack of social support, illnesses and sleep problems of the child, socio-economic status, or an unplanned/unwanted pregnancy [14–17]. Longitudinal studies from Sweden and the Netherlands found that parental stress in early parenthood was associated with anxiety during pregnancy as well as with postnatal depressive symptoms [18, 19]. Another risk factor for pre- and postnatal depression may be the experience of childhood trauma, like childhood sexual abuse [20]. Protective factors that seem to be associated with maternal health disorders are supportive couple's relationships [21] and breastfeeding [22], but are less well studied than risk factors.

As the first postnatal months are an important period for the child’s physical and mental development, studies have focused on how this development of the child is affected by poor maternal mental health [1, 23–25]. One negative consequence in early childhood seems to be an elevated vulnerability for regulatory problems, meaning problems of feeding, sleeping or excessive crying [26–28]. Population-based studies, which collected data on regulatory problems, assessed rates up to 21% within the first 2 years of life [29, 30]. A recent study from Germany reported rates of 10.1% for excessive crying, of 36.4% for feeding problems and of 12.2% for sleeping problems [31], with the first two regulatory problems seeming to be associated with maternal anxiety and the latter with maternal depression [28]. There are also studies indicating bidirectional effects of parental and children's mental health [32, 33]. Children with regulatory problems also seem to have an elevated risk for later psychopathological symptoms in the childhood period [34, 35]. But children of parents with mental health problems are not only at risk in the childhood period, indeed they seems to be at an elevated risk to develop poor mental health outcomes at some point in their lifetime, a concept called ‘trans-generational transmission’ [36–38].

Reasons for developmental problems of children with parents showing poor mental health in early childhood can in part be explained by an impaired parent-infant-relationship [39, 40]. Thus, therapeutic interventions should not only address parents or children separately, but must also focus on the parent-infant relationship [41]. One promising approach are specialized parent-infant psychotherapies [42, 43]. In Germany (like in other countries), there are out- and inpatient health care structures specialized in offering treatment for perinatal mental health disorders, for example mother-baby-units within psychiatric hospitals [44, 45] or specialized psychotherapeutic outpatient clinics [46, 47], offering parent–child psychotherapy. Another example are early support programs beginning directly after birth in the maternity ward, like the Babylotse Plus program for psychosocially burdened mothers and their infants [48]. To allow better access to psychosocial support for pregnant women and families with children aged 0–3 years, a public Early Childhood Intervention (ECI) program has been implemented in Germany in 2006 [49]. The program is open to all pregnant women and families with young children, with additional support for families in need. Services include home visits by health care professionals or volunteers and more intensive parenting programs to develop secure infant-parent attachment [49].

Even though there are specialized structures and programmes, knowledge of postnatal mental health service provision for parents seems to be insufficient. In Germany, a study by the National Centre of Early Prevention revealed a clear difference between educational groups in knowledge and use of assistance programmes supporting families with psychosocial burden [50]. A systematic review found that women experience barriers in seeking and receiving psychological and psychosocial interventions, for example for postnatal depression [51]. One obvious barrier seems to be the stigma associated with mental health disorders [51, 52]. There is little information on health care costs associated with postnatal mental health problems, because health economic data in this area has rarely been evaluated. A study from UK calculated total lifetime costs of perinatal depression to be £ 75,728 per woman with this disorder, most of it related to adverse impacts on the child [53].

Overall, more population-based epidemiological data on mental health in early childhood as well as information on health and social care service utilisation are needed to clarify the situation in Germany.

The collaborative German *SKKIPPI* project would like to make a contribution to this and includes an observational population-based cohort study as well as two interventional studies (https://skkippi.ipu-berlin.de/). The SKKIPPI intervention studies are randomized controlled trials (RCT) that will evaluate the efficacy of a specific parent-infant/toddler psychotherapy (6 week program according to a specific SKKIPPI Study Treatment Manual) compared to care-as-usual in mothers with mental health disorders and in mothers of children with regulatory problems, respectively. The two RCTs will be performed in Berlin (both RCTs), Flensburg (only RCT for mother with mental health disorders) and Leipzig (only RCT for mothers with children with regulatory problems), so within the same cities as the cohort study, but they will be described separately. Participants of the cohort study, which qualify for the interventional studies, are invited to take part in the RCTs. If they agree to participate, they will be excluded from the follow up assessment of the cohort study. SKKIPPI is performed within and funded by the German Health Care Innovation Fund, aiming at improving quality and integration of health care [54]. The present article focuses on the rationale, objectives, and design of the observational population-based cohort study as part of the SKKIPPI project.

The primary aim of the SKKIPPI cohort study is to assess the occurrence and course of psychosocial stress and mental health disorders in parents and their children in early childhood in three German regions. Furthermore, potential risk and protective factors as well as the use of health care and social service related to these disorders will be examined.

## Methods

### Objectives of the study

The objectives of the SKKIPPI cohort study are:i.To assess the occurrence of psychosocial stress and mental health disorders in parents and their children in early childhood.ii.To assess protective and risk factors for psychosocial stress and mental health disorders in parents and their children.iii.To assess the health care and social services utilisation and associated costs of parents with psychosocial stress and mental health disorders and their children [services based on German Social Security Code V (health care service: outpatient and inpatient sector) and services based on German Social Security Code VIII, IX, XII (Early Childhood Intervention program sector)].

### Design

The SKKIPPI cohort study is a prospective observational population-based cohort study with a two-step screening design.

### Sample characteristics

Parents with children aged up to 12 months (at the time the sample is drawn) will be recruited from three German cities: Berlin (3,600,000 inhabitants), Leipzig (560,000 inhabitants), and Flensburg (86,000 inhabitants). In these areas combined, annually almost 49,000 children have been born in recent years [55–57]. Out of all registered children aged 12 months and younger, a random sample of 30,000 contact addresses of the children's parents will be drawn from the residents' registration offices including 25,200 from Berlin, 4250 from Leipzig, and 550 from Flensburg, according to the proportion of births. We chose this approach to reach as many parents in the respective regions as possible. Parents are invited by postal letter to participate in the study. The focus of our study is on the mothers (biological and adoptive mothers), but fathers are encouraged to participate as well, to gain insights into their psychosocial stressors after birth and to identify further research needs. With an expected response of about 20% based on another German population study [58], about 6000 mother–child pairs are expected to participate in our study. For the screening step 1 mothers with children up to 2 and a half years are included. If the mother qualifies for follow-up assessment the children may be up to 3 years of age.

The inclusion criteria are:Mother or father (natural or adoptive) with a child up to the age of 12 months at the time of sampling, registered in Berlin, Leipzig, or FlensburgWritten or online informed consentParental age of at least 18 yearsParticipants are able to understand the German, English, Turkish, or Arabic language

### Procedures

To identify participants at risk, a two-step screening design will be implemented (Fig. 1). 30,000 potential participants receive an invitation letter, primarily addressing the mother, while fathers are also encouraged to participate in the screening step 1. In this first step, parental symptoms of psychological stress and signs of regulatory problems in the children will be assessed via online questionnaire.

**Fig. 1 Fig1:**
[figure not shown]
Flowchart SKKIPPI Cohort Study

While both mothers and fathers can participate in the first step, for the second step, only mothers will be included. As mothers are usually the main reference persons of the children in the first years of life, a significantly higher participation of them is expected. For this reason, we decided to assess mental health problems only in mothers and their children. Mothers who screened “positive” in the first step, meaning achieved at least 10 points in the online questionnaire, will enter the second step of the screening for a more in-depth assessment, where specially trained study staff will conduct phone interviews for mental health disorders (adapted version from the MINI [59]). In addition, questions on depressive symptoms, symptoms of parental burnout, symptoms of regulatory problems of the children, questions on childhood trauma of the parents, and detailed data on kind and frequency of health and social care utilisation will be collected (via telephone interview or online questionnaire).

After 6 months, a follow-up assessment will be performed with all mothers with a current mental health disorder (based on the MINI interview [59]) or a positive outcome in the Edinburgh Postnatal Depression Scale (EPDS) [5] or Parental Burnout Assessment questionnaire (PBA) [12] within the screening step 2 (“positive” screening step 2). The same data as in the screening step 2 stage will be collected, with additional data about the use of health care services and official support services in the last 6 months. We estimated that 80% of the participants would take part in the follow-up assessment.

### Endpoints

The primary endpoints of the cohort study are:i.*For mothers*: (i) presence of at least one current mental health disorder (based on the M.I.N.I interview [59]). (ii) presence of parental burnout symptoms (defined as score of ≥ 76 in the Parental Burnout Assessment questionnaire [12]). (iii) Presence of depressive symptoms (defined as an Edinburgh Postnatal Depression Scale (EPDS) score of 10–12 points (minor symptoms) or ≥ 13 points (major symptoms) versus 0–9 points (no symptoms) [5]ii.*For children*: presence of problems concerning crying, feeding and sleeping (so-called regulatory problems) (defined as a total score of ≥ 1.85 in the questionnaire on crying, feeding and sleeping disorders [60]). Subscales (crying, feeding and sleeping) will also be evaluated individually.

Secondary endpoints include:*For mothers*: presence of the following current mental health disorders: major depressive episode, major depressive disorder, manic and hypomanic episodes, panic disorder, agoraphobia, social anxiety disorder (social phobia), obsessive–compulsive disorder, posttraumatic stress disorder, alcohol use disorder, substance use disorder (non-alcohol), Anorexia nervosa, Bulimia nervosa, binge-eating disorder, generalized anxiety disorders.*For mothers and children*: health care and social services utilisation and costs: medical consultations, utilisation of midwifery care/physical therapy/speech therapy/occupational therapy, acute and rehabilitation hospital stays, utilisation of Early Childhood Intervention program components etc..

Additionally, the course and patterns of the observed disorders and problems will be evaluated by a follow-up assessment after 6 months. Potential risk and protective factors such as sociodemographic characteristics, marital, family, health, and work related stressors, critical life events, and pre-existing mental health disorders will be examined. If fathers agree to participate in the screening step 1, we will have the information of the latter also for the fathers.

### Instruments

#### Screening step 1

In the screening step 1, study participants fill out a short online-questionnaire. The questionnaire was developed with the aim of having a high sensitivity to detect potential mental health disorders and psychosocial stress. By implementing a two-step screening design we hope to reach a high sensitivity and high specificity, allowing an accurate early detection of stress or mental health problems in parents and their children. There are existing screening instruments like the Babylotse-Plus screening form [61] or the Heidelberg Stress scale [62], but they showed either a high sensitivity and low specificity [61] or only a moderate sensitivity [62].

The questionnaire for the screening step 1 (self-developed and adapted parts) contains questions regarding the parent’s health status: symptoms of depression and/or anxiety, obsessive–compulsive problems, abuse/addiction to alcohol/drugs, eating problems, lack of impulse control or mood swings, pre-existing mental health disorders. Questions regarding the child include the assessment of signs of crying, sleeping or feeding problems.

In addition, questions on sociodemographic characteristics, stress related to relationships, family and work, lack of social support and critical life events related to the pregnancy and child (for example an unplanned pregnancy or severe illness of the child) will be assessed. To reduce selection bias, the questionnaire was kept as long as necessary but as short as possible and in simple language, to achieve a high participation rate especially in those with a lower educational level or non-native German speakers. Otherwise, particularly those at risk for psychosocial stress and mental health disorders might be under-represented in the study. Therefore, either short questionnaires such as the Patient Health Questionnaire 4 [63] or individual questions from existing questionnaires were selected or adapted (the Crying, Feeding, Sleeping Questionnaire [60], the Zohar-Fineberg Obsessive Compulsive Screen [64], the Postpartum Bonding questionnaire [65], and the KID 0–3 questionnaire [66]). We developed a scoring system with points ranging from 0–5 for each question. The scores were discussed with a panel of experts from psychology, paediatrics, health sciences, and data sciences, taken into account cut-offs of included questionnaires. We piloted the questionnaire and adapted it as indicated (e.g. adding or rewording of response options). The scope of this pilot study was to test if the questionnaire was comprehensible, appropriate and feasible for the participants. Cut-offs were defined consensus based in order to identify a maximum of mothers with possible disorders, but the data from pilot study did not allow to conduct an in-depth analysis to calculate sensitivity or specificity. All mothers with an elevated score are invited to the screening step 2. This score was adjusted later on because the results of the first participants showed that too many mothers were included in the screening step 2 showing no current mental health problems. To increase the response among the major groups of parents with a migration background, all study documents of the screening step 1 were translated to English, Turkish, and Arabic.

#### Screening step 2

The screening step 2 (Table 1) includes the following questionnaires:Adapted version of the M.I.N.I. Version 7.02, a structured interview based on DSM-V and ICD-10 [59]. Suicidal and psychotic symptoms will only be assessed using an abbreviated version and are, therefore, not diagnostically interpretable. Modules on antisocial personality disorder and bipolar disorders were not considered, but major depressive episodes and manic/hypomanic episodes will be assessed separately.Parental Burnout Assessment (PBA) [12].Questionnaire on crying, feeding and sleeping disorders [60].Edinburgh Postnatal Depression Scale (EPDS) [5, 67].Questions on childhood trauma of parents [66].Questionnaires on the use of health care and psychosocial services (self-developed).

**Table 1 Tab1:** Screening steps and instruments

Screening step	Instrument
Screening step 1	Self-developed questionnaire on parental psychosocial stress symptoms and signs of regulatory problems in the children
Screening step 2	MINI [59]
Screening step 2	Parental burnout assessment [12]
Screening step 2	Edinburgh postnatal depression scale [5, 67]
Screening step	Questionnaire on crying, feeding and sleeping [60]
Screening step 2	Questions on childhood trauma of the parents [66]
Screening step 2	Self-developed questionnaire on health care and psychosocial service utilization

All interviewers will receive an intensive training based on Standard Operating Procedures (SOP). This training is focusing especially on the acquisition of interviews techniques to assess accurately mental health disorders using the M.I.N.I. interview [59]. After the formal training, each interviewer will do test interviews for several weeks under continuous supervision. Regular supervision of the interviewers will take place.

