### Statistical analysis

In the three recruitment areas of the cohort study (Berlin, Leipzig and Flensburg) almost 49,000 children have been born annually in recent years. A random sample of 30,000 children is drawn by the residents' registration offices, and their parents are invited to take part in the study. The response is estimated to be 20%; therefore, about 6000 mother–child pairs are expected to participate in the study. Assuming a prevalence of mental health problems in postnatal mothers of about 20% [8], a similar prevalence of regulatory problems in their children [68] and a considerable overlap of both problems, about 1,500 of the estimated 6,000 mother–child-pairs are expected to be included into the screening step 2 (Fig. 1). In the screening step 2, we estimate that about 1,200 participating mother–child-pairs with maternal mental health disorders and/or symptoms of regulatory problems in the child will be identified. For an occurrence of 20% of mental health disorders (1200 of 6000), a two-sided exact Clopper-Pearson 95%-confidence interval (95% CI) of 6000 participants has a width of ± 1% (i.e., 95% CI [19%; 21%]). This is considered sufficiently precise.

All data will be analysed descriptively. Results are presented in the form of means, standard deviations, medians and quartiles for continuous data, and frequencies and percentages for categorical data. Results (including occurrences) are reported with two-sided 95% CIs. Influencing factors for the presence of psychosocial stress or mental health disorders are analysed using logistic regression yielding odds ratios (OR) with 95% CIs and *p* values. Influencing factors or group comparisons for continuous variables (e.g. costs) will be analysed by linear regression or analysis of covariance (ANCOVA), yielding regression coefficients or means with 95% CIs and *p* values. All CIs and *p* values are two-sided and are interpreted exploratively (there is no formal significance level). Missing values are not replaced. All analyses are carried out with the respective available data (full analysis set).

For the cost analysis, the monetary valuation of the utilization of services is carried out by multiplying the frequency of utilization and corresponding standardized cost rates.

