## Preliminary results

By mid-March 2020 29,516 of the potential study participants received at least an invitation letter and at least one reminder. Overall, 4719 mothers and 889 fathers completed the screening step 1. Three participants were adoptive parents and three participants did indicate to be other caregivers (for example stepparents). So far, either the mother or the father or both parents of 4866 children (16.5%) have completed the screening step 1 questionnaire. All persons gave their informed consent prior to their inclusion in the study.

4472 participants came from Berlin, 75 from Flensburg, 933 from Leipzig and the remaining participants were living elsewhere at the time of the screening step 1. 811 participants were younger than 30 years, 4779 between 30 and 49 years and 21 participants 50 years or older (three values missing). 860 participants did indicate to be born outside Germany, 272 to be single parents and 2351 participants having more than one child.

Overall, 1139 mothers (24.1%) and 154 fathers (17.3%) screened so far “positive” in the screening step 1. As described above, only mothers with a “positive” screening step 1 are invited to the screening step 2.

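### The step-1 cut-off was changed after early step-2 results were seen; unless one rule is applied to all mothers, detected occurrence depends on how many were screened before the change

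*Protocol article*

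**What the plan says.** All references are to the protocol article.

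- **Methods, Instruments, Screening step 1.** The thresholds were set by expert agreement and aimed at catching as many cases as possible: "Cut-offs were defined consensus based in order to identify a maximum of mothers with possible disorders". Accuracy could not be checked beforehand: "the data from pilot study did not allow to conduct an in-depth analysis to calculate sensitivity or specificity". The text then says: "This score was adjusted later on because the results of the first participants showed that too many mothers were included" in step 2 although they had no current mental health problems. The original value, the date of change and the number of mothers screened before it are not given.
- **Methods, Procedures.** A positive step 1 means that the mother "achieved at least 10 points in the online questionnaire". No second value is mentioned.
- **Preliminary results.** 1,139 mothers (24.1%) were positive, reported as one count. The section adds that "only mothers with a “positive” screening step 1 are invited to the screening step 2".
- **Methods, Statistical analysis.** The planned occurrence is 1,200 of 6,000 (20%) with an exact 95% interval of 19% to 21%. All step-1 participants form the denominator, and each analysis uses whatever data are available.

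**The concern.** Step 2 supplies all the primary endpoints: the MINI interview, parental burnout, the EPDS and the child's crying, feeding and sleeping score. A mother who is not interviewed cannot become a case, but she stays in the denominator.

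The stated reason for the change implies that the threshold was raised. A mother scoring between the two cut-offs could then be detected early in recruitment, while a later mother with the same score could not. Combining both groups gives a numerator that depends partly on the timing of the change, which is not a property of the population. Entry to the six-month follow-up is affected in the same way, because it requires a positive step 2.

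The early interviews below 10 points are also the only verified data described in the article on what the final cut-off misses.

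**Working it through.** **1. The plan's own figure.** The Clopper-Pearson 95% interval for 1,200/6,000 is 18.99% to 21.03%, which reproduces the stated 19% to 21%. Observed positivity is 1,139/4,719 = 24.1%, against a planned 1,500/6,000 = 25%.

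**2. Difference between phases.** Let w be the share of mothers scoring between the two cut-offs and r the case rate among them. For identical populations, detected occurrence differs between phases by w × r. Neither value is in the article. Assumed ranges are w = 5–15% and r = 10–20%.

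- Low: 0.05 × 0.10 = 0.5 points
- High: 0.15 × 0.20 = 3.0 points

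**3. Shift in the pooled estimate.** If a share f was screened under the original rule, pooling raises the estimate above the uniform 10-point figure by f × w × r. It falls short of what the original rule would have detected by (1 − f) × w × r.

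| f (assumed) | Above uniform 10-point rule | Below original rule |
|---|---|---|
| 10% | 0.05–0.3 points | 0.45–2.7 points |
| 25% | 0.13–0.75 points | 0.38–2.25 points |

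At the upper end (w × r = 3.0 points), the pooled shift reaches the planned half-width of 1 point only if f is at least 1/3.

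**4. Cross-check through sensitivity.** Take the plan's 20% prevalence, with assumed sensitivity 0.95 and specificity 0.70 under the original rule, and 0.80 and 0.89 under the final rule.

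- Detected occurrence: 0.20 × 0.95 = 19.0% against 0.20 × 0.80 = 16.0%, a difference of 3.0 points.
- Pooled at f = 10%: 0.10 × 19.0 + 0.90 × 16.0 = 16.3%.
- Pooled at f = 25%: 0.25 × 19.0 + 0.75 × 16.0 = 16.75%.

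These are shifts of 0.3 and 0.75 points, in agreement with step 3.

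**5. Precision of a corrected estimate.** The add-back term is w × r, with r estimated from the m early mothers interviewed in the band. For illustration take N = 6,000, f = 10%, w = 10%, r = 15% and full step-2 participation, so m = 6,000 × 0.10 × 0.10 = 60.

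- Standard error of the add-back: 0.10 × √(0.15 × 0.85/60) = 0.46 points.
- Standard error of the main part at 20%: √(0.20 × 0.80/6,000) = 0.52 points.
- Combined half-width: 1.96 × √(0.46² + 0.52²) ≈ 1.4 points, against 1.0 without the correction.

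In this example the correction recovers 0.10 × 0.15 = 1.5 points of occurrence.

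**The case against.** The article does not say that the two groups will be pooled. The available-data sentence follows the rule that missing values are not replaced, and it reads as a missing-data rule. A single threshold and a single count near the planned 25% fit retrospective use of the 10-point rule as well as they fit a mixture. An analysis plan that is not shown may settle this. All of this stands, so the point has to be conditional. The two sections do not contradict each other either: one describes a change and the other gives the threshold in force.

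Several stronger readings are tempting and are not supported:

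- **Comparing 0.5–3.0 points with the ±1 point interval.** The first is a difference between phases and the second belongs to the pooled estimate. The comparable quantity is f times the difference, which is small if only a small early group was affected.
- **Distorted predictive value, or distorted comparisons by city, calendar time or child age.** Predictive value is not an endpoint, no such comparisons are specified, and nothing says that recruitment was staggered along those lines.
- **A change driven by maternal diagnoses alone.** The text speaks of mothers without current mental health problems. It does not say that nothing else was considered.
- **A change against the study's aim.** The two-step design is meant to reach high specificity as well as high sensitivity.

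One objection bears on the remedy. Simply dropping verified early cases below 10 points moves detected occurrence further from the truth. That is correct, and it is why those interviews must be used and not discarded.

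**Conclusion.** The concern holds in conditional form. A threshold for verification was changed after outcome data had been seen, and the article gives one rule and one unsplit count. Taken as written, the occurrence estimate would depend on f. The pooled shift is 0.05–0.3 points at f = 10% and 0.13–0.75 points at f = 25%, and it scales with f.

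This rests on four assumptions: the threshold was raised; the first participants belonged to the main study and not to the pilot, which the article describes separately as a feasibility test; and w and r lie in the assumed ranges. The true size cannot be found from the article. The occurrence shifts only if some cases score between the two cut-offs, but sensitivity is stated to be unknown, so the article gives no ground for calling the effect negligible.

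The point goes beyond a missing detail, because data already collected can both remove the dependence on phase and reduce the downward bias of the final rule.

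**What to change.** 1. State the original cut-off, the date of change, the number of mothers screened before it, and how many of the 1,139 positives arose under each rule.
2. Classify every mother by the 10-point rule from her recorded step-1 answers, and report detected occurrence on that uniform basis. This requires that the answers were kept item by item.
3. Keep the early step-2 interviews below 10 points. Estimate the rates of maternal disorder and of child regulatory problems by score, and add back the cases missed in that band. This assumes that early and later mothers with the same score are alike.
4. Report results by recruitment phase as a sensitivity analysis.

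The cost is modest extra analysis, a paragraph of reporting and a wider interval (about ±1.4 in place of ±1.0 points in the example above). Mothers below the original cut-off remain unverified, so the corrected occurrence should be presented as a lower bound.
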